##### Control Group

Parents in this group will be assessed (same measures as intervention group) at baseline and will have follow-up assessments at the same time as the intervention group (10 weeks, 6 months and 12 months post baseline assessment). These parents will be offered the intervention at 15 months post baseline assessment.

##### Measures

At recruitment, parents will be asked to complete an informed consent form confirming their participation in the study. All of the following measures will be administered at baseline, the end of the intervention, and at 6 and 12 months post intervention. The Demographic Questionnaire and Food Frequency Questionnaire for adults are the only exceptions, in that they will be administered at baseline and at 12 months post intervention only.

#### Primary outcome

##### Child eating habits and daily dietary intake

The Children's Eating Behaviour Questionnaire (CEBQ) will be used to assess child eating styles/habits, specifically, fussiness and responsiveness to satiety [40]. Typical food intake for children and their parents will be assessed using a semi-quantitative food frequency questionnaire [41] developed for Australian preschool children. The Eating and Physical Activity Questionnaire (EPAQ) is a two page document which asks specifically about foods which have been associated with obesity in the literature - particularly beverages, fruits and vegetables, processed snack foods and takeaway foods. Quantities are in general household measures and refer to either the previous day or typical intake. Standard serving sizes are based on the Australian Guide to Healthy Eating [42]. The EPAQ has been assessed against a 24-hour dietary recall in 90 parents of preschoolers and found to be valid [41]. Reliability has been found to be adequate [43]. This method of food recall has low participant burden and hence is both time and cost-efficient [44].

#### Secondary outcomes

##### Duration of daily child physical and sedentary activities

The Physical Activity Questionnaire for Preschool-aged Children (Pre-PAQ^®^) is a parent self-report measure that provides a list of 24 different types of physical and sedentary activities and requires parents to report on the time spent in the activities their child did "yesterday" and "last weekend" [45]. Parental proxy-reporting of their children's time-use has been used widely in developmental research [46-50], and has been shown to be a valid method of assessing individual differences in young children's time-use habits [51].

##### Parental knowledge of nutrition

Knowledge of child nutrition will be assessed with subscales of the Nutrition Knowledge Questionnaire [52].

##### Anthropometry

Height and weight will be measured with a stadiometer and standardised digital scales, respectively, at all assessments for children and at baseline, and at the 6 and 12 months follow up assessment time points for parents. Children and parents will be weighed each time wearing light clothing and no shoes. Height and weight measures will then be converted to a Body Mass Index (BMI, kg/m^2^) for each participant. Body Mass Index will be standardized for age and gender using BMI-for-age z-scores and change will be assessed using BMI z score slope [19] following WHO recommendations for children this age [53].

##### Parental behaviours and cognitions pertaining to feeding, eating and physical activity

**(1) *Maternal Child Feeding Patterns*: **The Preschool Child Feeding Questionnaire (PCFQ) [54] will measure mother's anxiety about feeding, responsibility for feeding, pressure to eat, and controlling feeding, and her concerns for her child's weight. The Child Feeding Questionnaire (CFQ) [55,56] will assess maternal restriction of access to food and monitoring of food. **(2) *Parental Eating*: **Typical daily food intake for parents will be assessed using the National Nutrition Survey Food Frequency Questionnaire [57]. **(3) *Parental modelling of physical and sedentary activities*: **The Active Australia Survey [58] (a validated questionnaire that measures physical activity behaviour in adults) will be used to measure parental engagement in physical and sedentary activities (duration and nature); this is retrospectively reported by parents for the last seven days. **(4) *Parental encouragement*: **Parents will also be asked to rate on a 5-point likert scale (1 = not at all encouraging; 5 = extremely encouraging) how encouraging they feel they are of their child participating in physical activities, eating fruits and vegetables, reading books, and watching TV; similarly, they will be asked to rate how discouraging they are of their child participating in sedentary activities, eating energy-dense snack foods and watching TV. **(5) *Parent cognitions*: **Parents will be asked to rate on a 5-point likert scale (1= not at all important; 5 = extremely important) how important it is to them that they are, and their child is, involved in sporting/physical activities, spends time reading, eats fruits and vegetables, socializes with other children, plays outdoors, plays indoors, and watches TV/DVDs, as well as how approving they both are of the television programs and videos their child views. **(6) *Parental concern for child weight*: **The concern for child's weight will be measured in the PCFQ [54]. **(7) *Child food neophobia*: **Pliner's Child Neophobia Scale [59] will be used to determine the extent of a child's reluctance to eat unfamiliar food.

### Qualitative interviews

We will invite 20 parents from the intervention to take part in an interview to obtain qualitative data in relation to barriers to creating a healthy home environment and the support or resources that parents find most useful in establishing and/or maintaining healthy behaviours and attitudes around diet and physical activity for themselves and their preschool child(ren). These interviews will take place 12 months post the intervention, and will inform us on the strengths of the intervention and subsequent program development.

### Power, sample size, and retention

The primary outcome for this intervention is child eating habits and dietary intake. Both the expected clinical effect of the intervention and variability of the primary outcome measure are important considerations. Thus, sample size calculations were based on Australian data by Mathews et al. that provide relevant parameter estimates from three studies in the Barwon-South Western region of Victoria (*n *= 950) with children aged 2-4 years of age [60]. Vegetable consumption will require the largest sample size to demonstrate change over time, compared to other dietary outcomes, such as sweetened drinks, packaged snacks (e.g., chips, muesli bar), confectionary/chocolate, cake/sweet biscuits, and fruit, based on sample size analyses. As there are no quantitative dietary recommendations for children less than 4 years old in Australia, we adopted Campbell et al.'s suggestion of a 25% increase in vegetable consumption as a minimum target [61]. Based on Mathews et al.'s finding that 63% of pre-school children had ≤1 serve of vegetables per day [60], we assume that the intervention will have a 25% absolute effect, that is the proportion of children in the intervention group who only have ≤1 serve of vegetables per day will change from 63% to 43%. We calculated the sample size necessary to detect a clinically meaningful difference in vegetable consumption, significant at the 0.05 level, with a power of 0.8; this calculation resulted in a sample of 100 parents in each group. Making a prudent allowance for attrition of 20% (attrition in a large longitudinal study with multiple time points over a 3-year period by Clark et al. [62]) the adjusted number per treatment condition is 120. A total of 240 parents of 2-4 year old children will therefore be recruited at baseline to allow for a final sample of 200. The final sample size of 200 participants is also sufficient to detect medium effect sizes in the secondary measures with a power of 0.8 at α = 0.05 [63]. Every CI on this research team has had experience in retention of participants in longitudinal studies. To facilitate retention we will build rapport with the participants by a regular newsletter and advance notification of assessments. To increase retention rates the CIs have found two measures are very helpful: 1) Parents who remain in the study will be entered into prize draws for gift vouchers. The amount needs to include a large grand prize plus multiple minor prizes. Prizes will be drawn each year. 2) Birthday cards will be sent out to each child participant.

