### Hypotheses

In comparison to the wait-list control group, we predict that at the completion of the 10-week intervention program, and at 6 and 12 months post intervention, the intervention group preschoolers will: (1) demonstrate greater consumption of fruit and vegetables, and a decrease in consumption of high fat, high sugar cordials, soft-drinks and juices and non-essential, energy dense snack foods; (2) exhibit less problematic eating habits, specifically higher responsiveness to satiety, less fussiness, and less neophobia; (3) demonstrate greater increases in physical activity and greater decreases in time spent in sedentary behaviours, specifically TV viewing; (4) exhibit lower BMI-for-age z scores.

In comparison to the wait-list control group, we hypothesise at the completion of the intervention program, and at 6 and 12 months post intervention, the intervention group parents will: (1) increase the frequency with which they limit the offering of high fat, high sugar cordials, soft-drinks and juices and non-essential, energy dense snack foods to their child; (2) increase the frequency with which they offer vegetables and fruit, water and milk (rather than cordials, soft-drinks and juices) to their child; (3) demonstrate improved knowledge regarding key aspects of child eating, physical activity and sedentary behaviours relevant to the prevention of obesity and improving child health generally; (4) reduce the frequency with which they use restrictive feeding practices and increase the frequency with which they use covert methods of controlling access to unhealthy foods; (5) increase the frequency with which they model healthy behaviours around diet and physical activity; (6) provide greater opportunities for children to engage in physical activity and reduce their opportunities for engagement in sedentary behaviours.

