
### Analyses

We will adhere to 'intention-to-treat' principles following CONSORT Statement guidelines to prevent introduction of systematic bias [34]. As such, baseline data will be secured prior to treatment allocation, missing values will be scrutinized to check for non-random distribution and primary analyses will be executed twice: once using observed data, and once using multiple imputation under multivariate normal assumptions using methods given by Schafer [64], so that all participants will be analysed in their allocated condition. Analyses of covariance (with "other relevant variables" from above as covariates) will test the between group differences in the primary and secondary outcomes at each assessment time point and across time points for the parents and children. Finally, the interview transcripts will be analysed using elements of phenomenology and thematic content analysis [65], as demonstrated by Clark et al. and Powell et al. [66,67].

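### The primary outcome is a multi-measure domain tested at three unranked time points, but the trial is sized at the full 0.05 on one binary vegetable variable never named as primary

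*Protocol article*

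**What the plan says.** - **Primary outcome.** The section Power, sample size, and retention states: "The primary outcome for this intervention is child eating habits and dietary intake". Under the Primary outcome heading, the CEBQ "will be used to assess child eating styles/habits, specifically, fussiness and responsiveness to satiety". The EPAQ covers foods linked to obesity, "particularly beverages, fruits and vegetables, processed snack foods and takeaway foods".
- **Time points.** The Hypotheses section predicts benefit "at the completion of the 10-week intervention program, and at 6 and 12 months post intervention", giving the three times equal standing.
- **Tests.** The Analyses section plans analyses of covariance for group differences "in the primary and secondary outcomes at each assessment time point and across time points for the parents and children". It adds that "primary analyses will be executed twice: once using observed data, and once using multiple imputation under multivariate normal assumptions". It gives no significance level, no testing order and no lead version.
- **Sample size.** The calculation uses the proportion of children with 1 serve or less of vegetables per day, 63% falling to 43%, at level 0.05 and power 0.8, and arrives at 100 per group. The reason for choosing this variable is: "Vegetable consumption will require the largest sample size to demonstrate change over time, compared to other dietary outcomes". The comparators listed are sweetened drinks, packaged snacks, confectionery, cakes/biscuits and fruit.

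**The concern.** What the article calls primary and what it sizes the trial for are different things. The primary outcome is a domain containing many variables, each examined at three times. The sized variable is one dichotomised food item, and no sentence makes it the primary endpoint.

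Two things are at stake. The first is the error rate: with several co-equal primary variables and visits, 0.05 per test is not the error rate of the trial's overall conclusion. The second is power: if that error rate is controlled across the domain, the stated sample no longer gives the stated power. The abstract's Discussion makes national implementation possible if the trial is positive, yet the article does not define which result would make it so.

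**Working it through.** **Inputs.** From Power, sample size, and retention: p1 = 0.63, p2 = 0.43, level 0.05, power 0.80, 100 per group after attrition. Sidedness is not stated; two-sided is assumed because it reproduces the stated number.

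**1. Reproduce the stated sample size.** With pooled variance under the null and p̄ = 0.53:

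n = [z(α/2)·√(2p̄(1−p̄)) + z(β)·√(p1(1−p1) + p2(1−p2))]² / (p1 − p2)²

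- √(2 × 0.53 × 0.47) = 0.7058
- √(0.63 × 0.37 + 0.43 × 0.57) = 0.6915
- n = (1.960 × 0.7058 + 0.842 × 0.6915)² / 0.20² = 96.6, so 97 per group

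This agrees with the stated 100. Other formulas give 94 (unpooled), 97 (arcsine) and 107 (continuity-corrected); one-sided gives 76. The 100 therefore matches the vegetable variable taking the whole two-sided 0.05.

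**2. Power at 100 per group if the level were shared.** Power = Φ[(0.20 × √100 − z(α/2) × 0.7058) / 0.6915].

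| Level | z | Power at 100 per group | Needed per group for 80% |
|---|---|---|---|
| 0.05 | 1.960 | Φ(0.892) = 81% | 97 |
| 0.05/8 = 0.00625 | 2.734 | Φ(0.101) = 54% | 158 |
| 0.05/24 = 0.00208 | 3.078 | Φ(−0.250) = 40% | 190 |

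The count of 8 is a reading of two sections together: 2 CEBQ scales plus the 6 dietary outcomes named in the sample-size section. Three visits give 8 × 3 = 24. Counting takeaway foods separately would raise it.

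**3. Chance of at least one false positive.** This assumes that any one component significant at 0.05 would be taken as success. The article does not state that rule. Independent tests give 1 − 0.95^k. The correlated values come from simulated normal test statistics, and the correlations are assumed because the article gives none.

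| Setting | Independent | With assumed correlations |
|---|---|---|
| 8 components, one visit | 34% | 30% (0.3 between components); 25% (0.5) |
| 8 components × 3 visits | 71% | 58% (0.3 between components, 0.6 between visits); 47% (0.5 and 0.7) |
| 1 component × 3 visits | 14% | 13% (0.5 between visits); 12% (0.6); 11% (0.7) |

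**4. The duplicate analysis.** The observed-data and imputed versions of one test are nearly the same test. At an assumed correlation of 0.90 to 0.95, the chance that either is significant under the null is about 7.0% to 6.5%. The added error is small; the open matter is which version leads.

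**The case against.** Multiplicity control, testing order and the lead missing-data analysis are often left to an analysis plan, and a journal article condenses its protocol. Their absence is not the finding. What stands is the mismatch in the text itself: a multi-measure primary outcome beside a calculation that spends the whole 0.05 on one variable. An unseen plan that divided the level by Bonferroni could not repair this at 100 per group, as the power table shows.

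A reader might infer that every test will be run at 0.05 and that any single significant result would make the trial positive. The article does not support this. The Analyses section states no level or decision rule, 0.05 appears only as a sample-size input, and the hypotheses predict benefit throughout rather than on any one item. The false-positive figures are therefore conditional.

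A reader might also infer that a conclusion could rest on a food item with inadequate power. The article answers this by stating that vegetables need the largest sample of the dietary outcomes. That covers the other foods at 0.05. It does not cover the CEBQ scales or the type I error. For the scales no target effect is given; at 100 per group and 0.05, a standardised difference of about (1.960 + 0.842) × √(2/100) = 0.40 has 80% power, so they are not shown to be underpowered either.

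Finally, imputation is linked to analysing all participants as allocated, which suggests, without saying so, that the imputed version leads.

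**Conclusion.** The point holds as a stated mismatch. The primary outcome is fixed as a domain tested at three unranked times and across time, while the sample size belongs to one binary vegetable variable that is not named as primary.

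The firmest figures concern power: about 81% at 100 per group if that variable takes all of the 0.05, 54% at 0.05/8 and 40% at 0.05/24. They rest on the article's own rates, a two-sided test and, for the last two, the count of eight components and a Bonferroni split.

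The false-positive range of 25–34% at one visit and 47–71% over three visits additionally needs the any-one-suffices rule and the assumed correlations. It shows what is possible if the matter stays open, not what the article prescribes. Even one component at three visits gives about 12%.

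**What to change.** Before outcome data are seen, state in the protocol and analysis plan:

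1. **One primary endpoint:** the proportion of children with 1 serve or less of vegetables per day on the EPAQ, already used for sizing.
2. **One primary time point.** Twelve months post intervention is one option, but the choice is the sponsor's. The 20% attrition allowance is not tied to any visit and does not decide it.
3. **One lead analysis**, suited to a proportion, since the article names only analysis of covariance. Multiple imputation fits the stated intention-to-treat aim; observed data then serve as sensitivity analysis.
4. **Everything else** (other foods, CEBQ scales, other time points) secondary, or tested in a fixed order after the primary.

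This keeps the level at 0.05 and about 81% power at 100 per group, with no added participants. The cost is wording, and the sponsor gives up claiming primary success on any other component. Keeping the bundle under a Bonferroni split would instead need 158 per group (8 tests) or 190 (24 tests), before attrition.

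### The planning effect is labelled 25% absolute, but the figures that give 100 per group are a 20-point (32% relative) fall, and the link to the 25% consumption target is not shown

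*Protocol article*

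**What the plan says.** All the relevant text is in one paragraph of the protocol article, Power, sample size, and retention.

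- The outcome being sized: "The primary outcome for this intervention is child eating habits and dietary intake". Vegetable consumption is chosen because it is said to need the largest sample among the dietary outcomes.
- The target: the authors adopt from a cited source the "suggestion of a 25% increase in vegetable consumption as a minimum target".
- The starting proportion, from a second cited source: "63% of pre-school children had ≤1 serve of vegetables per day".
- The planning effect in words: "we assume that the intervention will have a 25% absolute effect".
- The same effect in figures, joined to those words as their definition: the proportion of intervention children "who only have ≤1 serve of vegetables per day will change from 63% to 43"%.
- The error rates: "significant at the 0.05 level, with a power of 0.8". Sidedness is not given.
- The result: 100 parents per group, later raised to 120 for attrition.

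**The concern.** The label and the figures that define it disagree within one sentence. 63% minus 43% is 20 points, so the effect is not 25% absolute; nor is it 25% relative, since 20/63 is 31.7%.

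There is also a change of scale. The adopted target concerns how much is eaten. The calculation concerns the share of children at or below a threshold of one serve. The paragraph moves from one to the other without a conversion.

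This is the only sizing argument for the primary outcome. (For the secondary measures the section separately appeals to medium effect sizes.) If the effect is misdescribed, a reader cannot tell which effect the trial has 0.8 power to detect, and a null result could wrongly be taken to rule out the 25% target.

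**Working it through.** **Inputs from the protocol article:** control proportion p1 = 0.63; intervention proportion p2 = 0.43; alpha 0.05; power 0.80; equal groups; stated n = 100 per group. **Assumption:** a two-sided test, because sidedness is not stated.

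**Size of the effect as printed**
- Absolute: 0.63 − 0.43 = 0.20, which is 20 percentage points.
- Relative: 0.20/0.63 = 0.317, which is 32%.

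**Where a 25% effect on this proportion would end**
- 25 points: 0.63 − 0.25 = 0.38.
- 25% relative: 0.63 × 0.75 = 0.4725.

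**Formula** (pooled two-proportion), with d = p1 − p2, q = 1 − p, and p̄ the mean of p1 and p2:

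n = [1.96·√(2p̄q̄) + 0.8416·√(p1q1 + p2q2)]² / d²

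**Reproducing the stated 100 (63% v 43%).** p̄ = 0.53.
- √(2 × 0.53 × 0.47) = √0.4982 = 0.7058; times 1.96 = 1.383.
- √(0.2331 + 0.2451) = √0.4782 = 0.6915; times 0.8416 = 0.582.
- n = (1.383 + 0.582)²/0.04 = 3.863/0.04 = 96.6, so 97 per group.

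This is within 3% of the stated 100. An arcsine formula also gives 97. Other conventions give 94 (unpooled variance), 107 (continuity correction) and 76 (one-sided).

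**Same formula for the 25% readings**
- 63% v 38%: n = 61.6, so 62 (70 with continuity correction).
- 63% v 47.25%: n = 155.4, so 156 (168 with continuity correction).

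**Power at 100 per group:** Φ{[d√n − 1.96√(2p̄q̄)] / √(p1q1 + p2q2)}. For 63% v 43% this is Φ{(0.20 × 10 − 1.383)/0.6915} = Φ(0.89) = 0.814.

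| Reading | Proportions | n per group for power 0.80 | Power at 100 per group |
|---|---|---|---|
| Figures as printed: 20 points, 32% relative | 63% v 43% | 97 | 81% |
| 25 points | 63% v 38% | 62 | 95% |
| 25% relative | 63% v 47.25% | 156 | 61% |

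Only the printed pair gives about 100. The calculation used 20 points, and the 25% label did not generate the sample size.

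**The consumption target.** Power for a 25% rise in mean intake cannot be computed from the document, because it gives no mean, standard deviation or distribution for serves per day.

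**The case against.** The best defence is that this is a slip of labelling. Both proportions are printed straight after the label, so a reader can see what was powered, and 100 per group is right for them. That stands: the computation of 100 is not in error. It does not rescue the sentence, which still gives a wrong size for the planning effect, and it leaves the step from the 25% target to 63% v 43% unexplained.

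A reader might go further and infer that the trial is underpowered for its minimum target. The document does not support that. The word it uses is absolute, and on that literal reading (63% to 38%) 100 per group is more than enough, with 95% power. Power falls below 0.8 only if a relative reduction was meant, and the document never states that reading.

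A reader might also assume a count distribution for serves per day and derive low power for a 25% rise in mean intake. Any such figure would come from an assumption with no source in the document. It would also concern a dichotomised outcome, whereas the Analyses section plans analysis of covariance.

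Finally, the target comes from a cited source that is not at hand, so the mapping cannot be called wrong. It can only be called not shown.

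**Conclusion.** The point holds as an error in describing the planning effect, together with an unsupported link to the adopted target. The effect used is a 20-point (32% relative) reduction. For that effect, 100 per group gives about 81% power, assuming a two-sided 0.05 test and the pooled two-proportion formula. A 25% effect on this proportion would need 62 or 156 per group depending on the scale, with 95% or 61% power at 100. Power of 0.8 for the 25% consumption target is not established. Whether the true figure lies above or below 0.8 depends on what was intended. A shortfall in the sample size has not been demonstrated.

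**What to change.** In Power, sample size, and retention:

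1. Replace the 25% absolute label with a reduction of 20 percentage points (32% relative), from 63% to 43%, for which 100 per group gives about 81% power. State whether the test is two-sided.
2. Say how the adopted 25% rise in consumption translates into that change in proportion. If it cannot be justified, stop presenting the calculation as powering for that target.
3. If a 25% relative reduction was meant, say so and report that power at 100 per group is about 61%.

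The cost is a few sentences of protocol text and possibly a less favourable, but correct, statement of what the trial can detect. No change in enrolment is needed.

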#### Procedure

##### The Intervention

The MEND 2-4 program involves 10 weekly 90 minute workshops relating to general nutrition, physical activity and behaviours, that are typically held at community health and maternal and child health centres, where parents and their preschool-aged children attend together. Each program group will consist of 6-10 child-parent dyads and a MEND 2-4 trained program leader. Program leaders, who are trained extensively by MEND Australia prior to starting with a group, will be monitored and evaluated by MEND Australia staff to ensure their practice is in accordance with MEND 2-4 guidelines; parental feedback on program leaders will also be obtained. Each session involves 30 minutes of guided active play, where parents can learn how to play with their children; 15 minutes of healthy snack time based on an evidence-based exposure-based technique to promote acceptance and increased intake of fruit and vegetables [38] and 45 minutes where the children participate in supervised crèche-style, creative play activities and concurrently the parents attend an interactive education and skill development session, based on evidence-based group-based parent-training principles [39]. Table 1 outlines the weekly education topics, and parents will receive handouts on these topics weekly. Pilot data reveals low attrition and that parents value the program and attend all 10 sessions. In the initial MEND 2-4 trials (UK) the participation rate was 87.6% which is high for developmental research [35].

**Table 1 T1:** Discussion topics and intervention content of MEND 2-4 program

Week	Workshop Title	Discussion Topic(s)	Intervention Content
1	**Welcome & introduction**	Meet the leader and pre-program measurements	Meet and welcome the families to their first MEND 2-4 physical activity and snack-time session; parents complete all pre-program forms and questionnaires and accurate child and parent anthropometric measurements (height and weight) taken.

2	**Introduction**	Introductions and individual expectations	Discussion of individual expectations and introduction of MEND 2-4 program and practicalities; Introduction of parents/carers to the behavioural model of parenting (customised as the 4Cs model (Causes, Consequences, Consistency and Copying) for the purposes of MEND 2-4).

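### Group delivery in the intervention arm only has no allowance in the vegetable sample size or the named ANCOVA; how much this matters depends on an ICC the document does not give

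*Protocol article*

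**What the plan says.** Overall study design and Participants describe individual randomisation of parents, equally to MEND 2-4 or wait-list. Under The Intervention, families attend ten weekly workshops together: "Each program group will consist of 6-10 child-parent dyads and a MEND 2-4 trained program leader". Under Control Group, wait-list parents are offered the program only at 15 months after baseline, so they belong to no program group during follow-up.

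Power, sample size, and retention assumes that the share of children eating at most one serve of vegetables a day is 63% without the program and 43% with it. It then states: "We calculated the sample size necessary to detect a clinically meaningful difference in vegetable consumption, significant at the 0.05 level, with a power of 0.8", and "this calculation resulted in a sample of 100 parents in each group". A 20% attrition allowance follows: "the adjusted number per treatment condition is 120". No ICC, design effect or other clustering allowance appears. A further sentence claims power of 0.8 for medium effects in secondary measures with the final 200.

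In Analyses, analyses of covariance with covariates "will test the between group differences in the primary and secondary outcomes at each assessment time point and across time points". No program-group or leader term is named.

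**The concern.** Families in one program group share a leader, a venue, guided play, snack time and interactive parent training over ten weeks. Their outcomes may be correlated for those reasons, while outcomes of ungrouped controls have no such source of correlation. This is a partially nested design: individual randomisation, with clustering created by treatment in one arm.

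If the within-group correlation is positive and the analysis ignores it, the standard error of the treatment difference is too small and the test rejects a true null more often than 5%. If the analysis does allow for it, the effective size of the intervention arm is below 100 and power falls. The first consequence matters most here, because the abstract says that a positive trial could lead to use as a national program, and overstated precision favours a false positive.

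**Working it through.** **Inputs from the Protocol article.** 63% v 43%, alpha 0.05, power 0.8, 100 per arm analysed, 120 per arm recruited, 20% attrition, groups of 6-10 at delivery, ungrouped controls. **Assumed:** a two-sided test (it reproduces the plan's figure) and an ICC between 0.01 and 0.10, since none is given.

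**Step 1: reproduce the plan's figure.** The pooled two-proportion formula, with mean proportion 0.53, is

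n = [1.96 × √(2 × 0.53 × 0.47) + 0.842 × √(0.63 × 0.37 + 0.43 × 0.57)]² / 0.20² = 96.6, so 97 per arm.

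Power at 100 per arm is 0.814. The stated 100 is therefore an independent-observations figure, rounded up. The 120 is 100 × 1.2, which covers attrition only.

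**Step 2: group size in the analysed data.** The 6-10 dyads are at delivery. After 20% attrition this is 6 × 0.8 = 4.8 to 10 × 0.8 = 8, so about m = 5 to 8 analysed dyads per group.

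**Step 3: design effect, intervention arm only.** DE = 1 + (m − 1) × ICC.

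**Step 4: worked case, m = 8 and ICC 0.05.** DE = 1 + 7 × 0.05 = 1.35.
- Variance of the difference: 0.43 × 0.57 × 1.35/100 + 0.63 × 0.37/100 = 0.00331 + 0.00233 = 0.00564; SE = 0.0751.
- Power, unpooled: Φ(0.20/0.0751 − 1.96) = Φ(0.70) = 0.759.
- Power, pooled null variance: null SE = √(0.53 × 0.47 × 2.35/100) = 0.0765; Φ[(0.20 − 1.96 × 0.0765)/0.0751] = 0.747.
- Type I error of the unadjusted test: 2 × [1 − Φ(1.96 × √(2/(1 + DE)))] = 2 × [1 − Φ(1.808)] = 0.071.

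**Step 5: the range, 100 analysed per arm.**

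| ICC (assumed) | m | DE | Power, pooled / unpooled | Unadjusted type I error |
|---|---|---|---|---|
| 0.01 | 5 | 1.04 | 0.806 / 0.817 | 5.2% |
| 0.01 | 8 | 1.07 | 0.800 / 0.811 | 5.4% |
| 0.02 | 5 | 1.08 | 0.798 / 0.809 | 5.5% |
| 0.02 | 8 | 1.14 | 0.787 / 0.798 | 5.8% |
| 0.05 | 5 | 1.20 | 0.775 / 0.787 | 6.2% |
| 0.05 | 8 | 1.35 | 0.747 / 0.759 | 7.1% |
| 0.10 | 5 | 1.40 | 0.738 / 0.750 | 7.4% |
| 0.10 | 8 | 1.70 | 0.687 / 0.699 | 9.2% |

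These are normal approximations. A t reference with few groups lowers power a little further: at m = 8 and ICC 0.05, from 0.759 to 0.733. Simulated t-tests with group effects in one arm support the error formula: 0.067 at m = 8 and ICC 0.05, with 96 in that arm (formula 0.071).

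**Step 6: detectable difference at ICC 0.05.** (1.96 + 0.842) × SE, with SE = 0.0726 at m = 5 and 0.0751 at m = 8, gives 20.3 and 21.0 points. Roughly 20.5-21 points is a fair statement, against the planned 20.

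**Step 7: secondary measures.** Taking a medium effect as d = 0.5 (assumed), power with 100 per arm is Φ(0.5/√((1 + DE)/100) − 1.96): 0.94 with DE = 1, 0.90 with DE = 1.35 and 0.86 with DE = 1.70. All exceed 0.8.

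**The case against.** **The size is unknown, and may be small.** This stands. Without an ICC, a reader cannot conclude that the stated 0.8 and 0.05 fail outright. At ICC 0.01 the rounding from 97 to 100 absorbs the power loss and the error is barely above 5%.

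**Delivered group sizes overstate the effect.** This also stands. Applying 10 dyads per group to post-attrition numbers at ICC 0.10 gives power of about 0.66 and an error of 10.4%, but it assumes no losses within groups. A design effect on both arms would overstate the loss too (0.69 instead of 0.75 at m = 8, ICC 0.05), because controls are ungrouped.

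**Covariates may recover the power.** Possibly. If the baseline outcome were a covariate with correlation 0.3 (both assumed), the variance would shrink by a factor of 1 − 0.09 = 0.91. At ICC 0.05 and 6.7 analysed dyads per group, SE falls from 0.0740 to 0.0706 and power is about 0.81. The plan does not state this gain, and it would not cure the type I inflation.

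**A fuller analysis plan may add a group term.** It may. The article's silence does not show that the final model ignores groups, or that group membership goes unrecorded. But the sample size is fixed in this document without a clustering allowance. A later group term would correct the error rate and leave the power statement as it is.

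**Conclusion.** The point holds in conditional form. The design is partially nested, the vegetable sample size is an independent-observations figure, and the ANCOVA as named has no program-group term. Followed as written, the unadjusted test exceeds 5% for any positive ICC, slightly at 0.01 and by about one to two percentage points at 0.05. The vegetable power is essentially intact at 0.01, about 0.75-0.79 at 0.05 and about 0.69-0.75 at 0.10. These figures rest on the assumed ICC range, on 5-8 analysed dyads per group and on 100 analysed per arm.

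A reader might infer that both power statements in the article fail. They do not: the one for medium effects in secondary measures keeps its 0.8 across this range. Error inflation, by contrast, is not confined to vegetables.

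**What to change.** - **Analyses:** specify a partially nested mixed model, with a random program-group effect in the intervention arm only, controls as singletons and small-sample degrees of freedom. Use a logistic version for the binary vegetable outcome.
- **Data:** keep the program-group ID for every intervention dyad.
- **Power, sample size, and retention:** state an ICC range with its basis, and restate power or the detectable difference for vegetables. At ICC 0.05 that is about 75-79% power for 20 points, or 80% power for about 20.5-21 points.

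The cost is analysis wording and one retained variable. Confidence intervals become slightly wider and the stated power slightly less favourable. No extra participants are needed, provided the lower power is stated openly.
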